##### Endothelial function

Endothelial function may potentially represent a quantitative method to assess the presence and extent of childhood cardiometabolic risk before the development of overt disease [40]. Flow-mediated dilation will be measured with the technique introduced by Ramírez-Vélez [41] in the Colombian population, using the guidelines reported by Corretti et al. [42]. The diameter of the brachial artery will be assessed using a high-resolution ultrasound device (Mindray M-9®, Shenzhen, China), equipped with a 7.5–10 MHz linear array transducer and an integrated electrocardiography package. B-mode images were obtained at a reproducible point in the distal third of the upper arm. Endothelium-dependent vasodilation was assessed by measuring flow-mediated dilation after 5 min of forearm ischemia [43]. All measurements will be taken at the end of diastole as observed by electrocardiogram (ECG). Briefly, a 1-min baseline measurement will be taken and then a pneumatic rapid cuff inflator (Hokanson, Bellevue, WA), placed around the forearm distal to the humeral epicondyle, will be inflated to 220 mmHg for 5 min. Recording of the image will be ceased on inflation of the cuff and recommenced 30 s before deflation. Peak dilation during each study will be defined as the greatest percentage change from the resting baseline brachial artery diameter. The intra-session coefficients of variations will be ≤1% for the baseline diameter. Reliability, estimated by intra-class correlation coefficients based on four baseline measurements (*n* = 8 subjects), showed an intra-class correlation coefficient of 0.91 for the baseline diameter and 0.83 for flow-mediated dilation (unpublished observations). Images will be recorded on a DVD player for subsequent measurements by one observer blinded to the study.

##### Carotid intima-media thickness

The carotid intima-media thickness (cIMT) will be assessed using semi-automated B- and M-mode ultrasound, (Mindray M-9®, Shenzhen, China) with a high-frequency linear-array probe (5–13 MHz) [44]. In brief, the left and right common carotid arteries will be imaged at a standardized magnification (2 × 2 cm). A participant’s head will be turned 45° away from the site being scanned. Optimal images will be captured at the end of diastole, incident with the R-wave of the ECG, for later analysis. Our inter-observer intra-class coefficient for cIMT measurements is 0.99 (coefficient of variation 0.99%) and the intra-observer intra-class coefficient for cIMT measurements is 0.98 (coefficient of variation 1.9%) (unpublished observations).

##### Anthropometric measures

Variables will be collected at the same time in the morning, between 7:00 and 10:00 a.m., following an overnight fast. The body weight of the subjects will be measured when the subjects are in their underwear and not wearing shoes, using electronic scales (Tanita® BC544, Tokyo, Japan). Height (using a stadiometer, Seca® 213, Hamburg, Germany), waist circumference, and hip circumference will be measured in centimeters using a tape measure (Ohaus® 8004-MA, Parsippany, NJ, USA). The waist circumference is measured as the smallest circumference around the torso between the end of the xiphisternum and the top of the iliac crests. The hips are measured at the greatest circumference between the iliac crests and the upper femur. Body mass index (BMI) will be calculated as the body weight in kilograms divided by the square of the height in meters. BMI will be classified as underweight, normal weight, overweight, or obese using the World Health Organization criteria [45]. The anthropometric measurements will be conducted by a nutritionist in accordance with International Society for the Advancement of Kinanthropometry guidelines [46]. The mean of three consecutive measurements will be recorded.

##### Body composition

We will also measure fat mass, lean body mass, and subcutaneous abdominal fat by conducting a dual-energy X-ray absorptiometry (DEXA) scan (HOLOGIC, QDR 4500 W). Visceral fat volume will be measured by bioelectrical impedance. An experienced DEXA technologist blinded to the study randomization will perform the DEXA imaging studies. The mean precision of our machine is 1.1% for soft tissue (unpublished observations).

##### Physical fitness

Physical fitness includes cardiorespiratory fitness, muscular strength, speed and agility, and flexibility. Moreover, physical fitness has been reported as a powerful marker of health in childhood, and its inclusion in the definition of metabolic syndrome has been proposed [47]. Cardiorespiratory fitness will be measured using the 20-m shuttle run test as previously described by Léger et al. [48]. The cardiorespiratory profile will be derived by computing standardized values of the number of completed laps performed by each participant by age and sex. Upper-body isometric strength (handgrip strength test) will be assessed using a handgrip dynamometer, (T.K.K. 5001, Grip-A, Takei, Japan), adjusted by sex and hand size for each adolescent [49]. The participants will be instructed to stand with their arms completely extended, squeezing the handgrip gradually and continuously up to the maximum of their strength, for at least 2 s, performing the test twice, alternating hands. The best score for each hand will be recorded in kilograms. The handgrip score (kg) will be calculated as the average of the left and right grip strength and then expressed per kilogram of body weight [50]. Lower-body explosive strength (standing long jump test) will be tested in an indoor gymnasium with a wooden floor. The adolescents will be instructed to push off vigorously from the starting line to jump as far forward as possible while landing on both feet and staying upright [51]. The test will be done twice, and the best attempt will be recorded. The standing-jump score will be determined by the distance between the last heel mark and the take-off line. The results of the handgrip strength and standing long jump tests will be transformed into standardized values (*z* scores) by age and sex. The *z* scores of the two tests will be added together to yield the muscular fitness score. Speed and agility (movement speed, coordination, and agility assessment) will be measured using the 4 × 10 shuttle-run test. The time that it takes to complete the test will be recorded to the nearest tenth of a second [52]. Flexibility will be measured according to the standard sit-and-reach test for range of movement (in cm).

##### Resting blood pressure and heart rate

An automated device will measure resting HR and blood pressure. Participants will be instructed to rest for 10 min prior to the measurement. HR and blood pressure will be measured twice from the dominant arm while the subject is in a supine position. This will occur at the initial screening visit and 30 min after training.

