**Methods/design:**

Altogether, 100 hundred overweight/obese, sedentary adolescents (aged 11–17 years) attending two public schools in Bogotá, Colombia, will be included in a parallel-group randomized controlled trial. Adolescents will be randomly assigned to an intervention group following one of four curricula: (1) the standard physical education curriculum (60 min per week of physical activity, *n* = 25) at low-to-moderate intensity; (2) a high-intensity physical education curriculum (HIPE, *n* = 25), consisting of endurance and resistance games and non-competitive activities, such as running, gymkhanas, lifting, pushing, wrestling, or hauling, for 60-min sessions, three times per week, with an energy expenditure goal of 300 to 500 kcal/session at 75–85% maximum heart rate (HRmax); (3) a low-to-moderate intensity physical education curriculum (LIPE, *n* = 25) consisting of endurance and resistance games and non-competitive activities (e.g., chasing, sprinting, dribbling, or hopping) for 60-min sessions, three times per week with an energy expenditure goal of 300 kcal/session at 55–75% HRmax; and (4) a combined HIPE and LIPE curriculum (*n* = 25). The HIPE, LIPE, and combined interventions were performed in addition to the standard physical education curriculum. The primary outcome for effectiveness is liver fat content, as measured by the controlled attenuation parameter 1 week after the end of the intervention program.

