#### Standard physical education curriculum

This is the control group (*n* = 25). These subjects will not carry out any intervention different from the physical education class prescribed by the Colombian education legislation (Legislation 115 of 1994, decree 1860 of 1994) [29], which is recognized as fundamental and is consequently obligatory in all educational institutions in the country. This session includes 60 min per week of physical activity at low-to-moderate intensity. However, during this period, education will be offered in lifestyles, hygiene, and diet [30] at no cost to participants. Nutritional counseling will be offered as well.

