### Data collection and outcome measures

Outcome measures will be assessed at baseline and at the end of the 6-month intervention by personnel blinded to the treatment allocation. Data will be recorded on standardized forms and entered into a secured Access database that contains quality control checks (e.g., range checks and notifications for missing data) (Fig. 2). Post-intervention measurements will be scheduled within 7 days following the last exercise session or last supervised program session in the exercise and control groups, respectively.

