**Fig. 2 Fig2:**
[figure not shown]
Schedule of enrolment, intervention, and assessment in the HEPAFIT study, according to the SPIRIT 2013 statement

The primary outcome measure is hepatic fat content, which will be assessed with the controlled attenuation parameter. The secondary outcomes of this study will test the additional effects of exercise training on traditional cardiometabolic risk factors [body composition, blood pressure, glycohemoglobin (HbA1c), serum lipids, and insulin resistance] and non-traditional cardiometabolic risk factors (visceral adiposity, endothelial function, cytokines, adipokines, aminotransferases, inflammatory biomarkers, uric acid, ferritin, albumin, and cardiorespiratory and muscular fitness). Also, we include neuronal function biomarkers as measured by neurotrophin-3 (NT-3), neurotrophin-4 (NT-4), and brain-derived neurotrophic factor (BDNF) levels (second secondary objective). Finally, attention capacity and psychological measurements will be assessed to evaluate the additional effect of the exercise intervention on the executive function, quality of life, self-esteem, and well-being of overweight and obese participants. Other covariables of interest include pubertal development, physical activity levels, sedentary behavior, dietary assessment, demographic characteristics, and side effects (Table 2).

**Table 2 Tab2:** Overview of the measurements and methodology at baseline and post-test in the HEPAFIT study

Measure	Methodology
Primary outcome	
Hepatic fat (%)	Vibration-controlled transient elastograph
Secondary outcomes	
Body mass (kg)	Scale
Height (cm)	Stadiometer
Waist circumference (cm)	Non-elastic tape
Blood pressure	Oscillometric monitor device
Heart rate	Oscillometric monitor device
Lean mass (kg), total body fat (%), bone mineral density (g/cm^2^), abdominal adiposity (g), truncal adiposity (g), limb adiposity (g)	Dual X-ray absorptiometry
Visceral adiposity (cm^2^)	Bioelectrical impedance
High-density lipoprotein cholesterol (mg/dL), low-density lipoprotein cholesterol (mg/dL), total cholesterol (mg/dL), total triglycerides (mg/dL), serum glucose (mg/dL)	Enzymatic spectrophotometry
Serum insulin (mU/L)	Electrochemiluminescence immunoassay
Glycohemoglobin (mg/dL)	Electrochemiluminescence immunoassay
Alanine (U/L), aspartate (U/L), gamma-glutamyl transferase (U/L)	Enzymatic assay
Uric acid, albumin (mg/dL), ferritin (mg/dL)	Enzymatic assay

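### Resting blood pressure and heart rate are timed 30 minutes after an unspecified training session, which is not reconciled with the 6-month post-test and could add an acute exercise response to the between-arm contrast

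*Protocol article*

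**What the plan says.** The section on resting blood pressure and heart rate describes duplicate supine readings with an automated device. On preparation it says "Participants will be instructed to rest for 10 min prior to the measurement". On timing it says "This will occur at the initial screening visit and 30 min after training". No other sentence in the article gives timing specific to these two variables.

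The section on data collection and outcome measures sets the general schedule: "Outcome measures will be assessed at baseline and at the end of the 6-month intervention by personnel blinded to the treatment allocation". It then fixes the window: "Post-intervention measurements will be scheduled within 7 days following the last exercise session or last supervised program session in the exercise and control groups, respectively".

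Blood pressure is named among the secondary outcomes, within "traditional cardiometabolic risk factors [body composition, blood pressure, glycohemoglobin (HbA1c), serum lipids, and insulin resistance". Table 2 lists both blood pressure and heart rate under secondary outcomes. The statistical analysis section treats primary and secondary outcomes as measured twice, at 0 and 6 months, and compares them across the four groups.

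**The concern.** The variables are labelled resting and are analysed as 6-month changes. Their own section gives two occasions: a screening visit, and a time defined by its closeness to a training session. The analysis section also has two occasions, so the natural reading is that the post-training value serves as the 6-month value.

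On that reading, the two values being compared are taken under different conditions. The first is not tied to exercise and the second falls in the recovery period after a session. What happens in recovery need not be the same in each arm, because the sessions differ. A between-arm difference in blood pressure or heart rate could then reflect the last bout of exercise as well as six months of the program. Randomization and blinded assessors do not protect against this, because the difference arises from the measurement conditions. With one follow-up value per participant, neither the mixed model nor the generalized estimating equations can separate the two components.

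**Working it through.** The documents state no effect size, standard deviation or power for blood pressure or heart rate, so there is no figure to reproduce. The check compares the passages and then shows the form of the possible bias.

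**1. The passages side by side**

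| Item | Resting blood pressure and heart rate section | Data collection section | Statistical analysis section |
|---|---|---|---|
| First occasion | Initial screening visit | Baseline | 0 months |
| Second occasion | 30 min after training | End of the 6-month intervention, within 7 days of the last session | 6 months |
| Which session | Not stated | Last exercise session (exercise arms); last supervised program session (control) | Not applicable |
| Control arm | Not stated | Included | Included |
| Minimum gap after exercise | Fixed at 30 min | None | Not applicable |

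A reading 30 minutes after the final session falls inside a window of 7 days. The two rules can therefore both be met, and when they are, the post-test is a recovery reading. The 10-minute rest does not change this: nothing says that it comes on top of the 30 minutes, and it is far shorter than a return to baseline conditions on another day would be.

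**2. Are the sessions alike across arms?** The intervention section gives these intensities:

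- HIPE: 75–85% of maximum heart rate, three 60-minute sessions a week.
- LIPE: 55–75% of maximum heart rate, three 60-minute sessions a week.
- Combined arm: elements of both programs.
- Control: the standard class only, described as follows: "This session includes 60 min per week of physical activity at low-to-moderate intensity".

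Equal acute responses cannot be assumed. The section on blinding and randomization methods also contrasts the control group with the exercise training groups, so it is unclear what a time after training means for a control participant.

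**3. Form of the bias.** Let θ be the 6-month effect in an arm and *a* the acute post-session response at the time of the follow-up reading. Take the acute component at screening as zero. Then

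expected change in an arm = θ + *a*

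expected contrast, exercise minus control = (θ_E − θ_C) + (*a*_E − *a*_C).

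The second bracket vanishes only if the acute responses are equal or absent. The same holds for HIPE against LIPE.

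**4. Illustration of size.** The inputs are 25 per arm (sample size section), two-sided α = 0.05, θ_E = θ_C, and an assumed acute difference δ in SD units. Neither δ nor the SD comes from the documents.

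SE = √(2/25) = 0.283 SD

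P(reject) = Φ(δ/SE − 1.96) + Φ(−δ/SE − 1.96)

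For δ = 0.5, δ/SE = 1.768, so P = Φ(−0.192) + Φ(−3.728) = 0.424.

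| Assumed δ (SD) | False-positive rate |
|---|---|
| 0 | 5% |
| 0.10 | 6% |
| 0.25 | 14% |
| 0.50 | 42% |
| 0.75 | 76% |
| 1.0 | 94% |

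The calculation assumes full retention and a simple two-group comparison, not the planned mixed model. Its result depends wholly on δ.

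**The case against.** The strongest reply is that the post-training reading may not be the analysed value at all. The sentence does not name the session, so it could describe a check made around individual sessions. The data collection section, the Table 2 heading, the later section on blinding and randomization and the analysis section all place outcomes at the beginning and end of participation. This stands as far as it goes: the biased reading is plausible but not established. It does not remove the need for a correction. If the sentence describes a per-session check, the section on resting readings does not say how the post-test value is obtained, and the text should say that the check is not the outcome.

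Several stronger readings are tempting, and the documents do not support them.

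- A reader might infer that only the training arms are affected, or that controls have no session to which a reading could be tied. The post-test rule names the control group and its last supervised program session, and controls attend a weekly class. The supported statement is narrower: the section on resting readings gives no control-arm equivalent.
- A reader might infer that the acute response is reported in place of the 6-month effect. It would be added to that effect.
- A reader might extend the concern to insulin resistance, triglycerides or flow-mediated dilation, because the 7-day window has no minimum gap. Blood is drawn early in the morning after a 10-hour fast, while the program runs at the end of the school day, so a 30-minute effect does not carry over to blood outcomes. A next-day effect on any of these outcomes is conjecture on these documents.
- A reader might cite the abstract's timing, "as measured by the controlled attenuation parameter 1 week after the end of the intervention program", as a further conflict. That phrase concerns liver fat and has no bearing on blood pressure or heart rate.

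**Conclusion.** The point holds in limited form. The timing sentence for resting blood pressure and heart rate does not identify the session or the control-arm equivalent, and it is not reconciled with the 6-month post-test at which these outcomes are compared. Followed as written, it adds any between-arm difference in acute post-session response to the 6-month contrast. The arms' session intensities give reason to expect that the responses may differ.

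The size and direction of that difference are not in the documents. The range of 6% to 94% shows only how sensitive the contrast would be to assumed differences of 0.10 to 1.0 SD; it is not an estimate for this trial. The conclusion rests on the post-training reading being the analysed follow-up, which is the natural reading but not the only one. Two secondary variables are affected. The liver fat outcome and the sample size are not. The change should be made, because an analysis plan cannot repair readings taken under unequal conditions.

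**What to change.** Rewrite the timing sentence to agree with the data collection section. Resting blood pressure and heart rate should be measured in all four arms at baseline and at the same post-test visit, under the same conditions on both occasions and not shortly after a session. State the interval from the last session, of whatever kind, and make it the same in every arm. If a reading 30 minutes after a session is still wanted, describe its purpose separately and state that it does not enter the outcome analysis.

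The cost is protocol wording and a few minutes at a post-test visit that is already planned. No extra visit is needed.

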##### Attention capacity

The d2 test of attention is a paper and pencil test that consists of 14 different lines of 47 randomly mixed letters (“p” or “d”). Briefly, for each line, the adolescents will be given 20 s to identify and mark the letter “d” when it is presented with two dashes placed above and/or below it (i.e., relevant elements). The remaining combinations are considered irrelevant elements. After 20 s, there is an acoustic signal, which prompts the participants to progress to the next line. Their attention capacity will be calculated as the number of correct relevant elements minus the number of irrelevant elements marked. The score will be transformed into age-specific percentiles. Thus, a higher attentional ability is indicated by a higher score [53].

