## Methods/design

### Study design, setting, and participants

The HEPAFIT study is a single-blind parallel-group randomized controlled trial (ClinicalTrials.gov ID NCT02753231). All parents or guardians will provide informed written consent and all the adolescents must give assent before being enrolled in the study. The study received ethical approval from the Medical Research Ethics Committee of the University of Rosario (ID UR-21042016). Random allocation to treatments will be performed at the individual level.

The study will include 100 adolescents (50% females) between 11 and 17 years of age attending to two public schools in the urban area of Bogotá D.C., Colombia. Inclusion criteria include primary overweight/obese status, defined according to the International Obesity Task Force [28], inactivity (no habitual participation in exercise more than once a week in the previous 6 months), and having at least one parent or caregiver willing to participate in the program sessions. Adolescents eligible for the present study will be invited to a pre-test, which will include a medical interview at the Centre for Studies of Physical Activity Measurements (in Spanish, CEMA), School of Medicine and Health Sciences, University of Rosario, Bogotá, Colombia. Risks will be minimized by identifying contraindications to the testing and training protocols via a health history and a thorough physical examination prior to the testing sessions. The exclusion criteria include having a clinical diagnosis of cardiovascular disease, having type 1 or type 2 diabetes mellitus, being pregnant, using alcohol or drugs, and not having lived in Bogotá for at least one school year. Adolescents with other causes of liver disease in the pediatric population that produce elevated liver enzyme levels will be excluded. These will be identified by screening for hepatotropic viruses (hepatitis A, B, and C, cytomegalovirus, and Epstein–Barr virus) and alpha-1 antitrypsin (A1AT) levels as well as autoantibodies and immunoglobulin G to rule out A1AT deficiency and autoimmune hepatitis, respectively. This study aims to investigate the effects of these interventions on risk factors for type 2 diabetes (i.e., its focus is prevention) rather than looking at their effects on treatment outcomes. Therefore, participants with established type 2 diabetes are excluded.

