##### Stroop task test

We will use the New Stroop Test II (Spanish version). This test measures selective attention, cognitive flexibility, and processing speed. It is used to evaluate executive function [54]. The test consists of two control tasks: a Stroop task and a reverse Stroop task. The number of correct answers, reverse-Stroop interference rate, and Stroop interference rate will be calculated.

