### Statistical analysis

The final data will be analyzed using IBM SPSS 22.0 (SPSS, Inc., Chicago, IL, USA) and SAS software (SAS Institute Inc., Cary, NC, USA). An exploratory analysis will be performed to determine the frequency, range, variability, and distribution type for each variable to establish the most appropriate statistical test when comparisons are necessary. These analyses will assess the primary outcome (hepatic fat) and will be undertaken using the intention-to-treat principle. The intention-to-treat analysis for this study will include all participants, including those who are not fully compliant and those with missing outcome data.

Because this is an experimental design with the primary and secondary outcomes measured twice, the first at baseline (*t*_0_ = 0 months) and the second after the interventions (*t*_1_ = 6 months), for four study groups, a comparative analysis between the measurements will determine the differences. A linear mixed model with repeated observations will be used for these comparisons, when appropriate, for each dependent variable. Subsequently, a multivariate analysis will be carried out, and the autocorrelation between repeated measures will be taken into account. We will use longitudinal analysis methods, such as a generalized estimating equation approach, to control the differences among measurements at baseline and to incorporate incomplete observations into this analysis. Pearson correlations will be calculated between the maximal values of the primary and secondary outcomes. Finally, we will investigate whether there is an interaction between the two interventions for the primary outcome after 30–40 min of supervised HIPE and LIPE or combined training (HIPE + LIPE). For these analyses, we will include appropriate interaction terms in the models [60]. We plan to report regression coefficients for the interaction terms and their 95% confidence intervals.

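### Converting the d2 attention score to age-specific percentiles puts one secondary outcome on a bounded, non-linear scale before a linear model; modelling the score itself would recover some precision at almost no cost

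*Protocol article*

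**What the plan says.** The protocol article's section on attention capacity defines the d2 result as the "number of correct relevant elements minus the number of irrelevant elements marked", which is a count difference. It continues: "The score will be transformed into age-specific percentiles".

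The section on data collection and outcome measures gives the purpose: "attention capacity and psychological measurements will be assessed to evaluate the additional effect of the exercise intervention on the executive function". Table 2 lists the d2 among the secondary outcomes.

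The statistical analysis section states: "A linear mixed model with repeated observations will be used for these comparisons, when appropriate, for each dependent variable". Before that, each variable's distribution is explored "to establish the most appropriate statistical test when comparisons are necessary".

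Neighbouring measures are treated differently. For the Stroop test, "The number of correct answers, reverse-Stroop interference rate, and Stroop interference rate will be calculated", with no percentile step. Cardiorespiratory fitness is derived by "computing standardized values of the number of completed laps performed by each participant by age and sex", and the strength tests become z scores by age and sex.

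**The concern.** Some age referencing is reasonable, since participants are "between 11 and 17 years of age". A percentile, however, does more than remove age. It is squeezed between 0 and 100, and it compresses differences in both tails relative to the middle. Two pupils who improve by the same amount can contribute very different changes.

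If percentiles enter a linear model, the estimated group difference mixes the exercise effect with the position of the sample on the norm curve, so it is hard to compare with another sample. Part of the information in the score is also lost, and with 25 per arm there is little to spare. The article states this choice of scale, so it is not a detail left for a later document to supply.

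**Working it through.** **What can be reproduced.** The article gives no power, effect size, SD, baseline level or correlation for d2. Its sample size section rests on hepatic fat alone, so there is no d2 figure to reproduce.

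**Inputs.** From the article: 25 per arm. Assumed: normally distributed scores and norms, a true effect of 0.5 SD, a pre-post correlation of 0.5 to 0.8, a two-sided 5% test and no dropout.

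**Step 1: what an equal gain is worth.** For a pupil starting at z, the percentile gain is 100 × [Φ(z + 0.5) − Φ(z)].

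| Start (SD from norm median) | −1.5 | −1 | −0.5 | 0 | +0.5 | +1 | +1.5 |
|---|---|---|---|---|---|---|---|
| Percentile points for a 0.5 SD gain | 9.2 | 15.0 | 19.1 | 19.1 | 15.0 | 9.2 | 4.4 |

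**Step 2: the best case.** For small effects in a sample that matches the norm, the efficiency of the mean percentile relative to the mean z score is [E φ(Z)]² ÷ (1/12) = 12/(4π) = 3/π = 0.955. That is a sample-size penalty of about 4.5%.

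**Step 3: power with baseline adjustment, no retest gain.** Two arms of 25 were simulated, 10,000 trials per cell, with follow-up compared by ANCOVA on the baseline. Entries are power (%) on the standardised score → power on its percentile, with the loss in points in brackets.

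| Correlation | Sample at −1 SD | −0.5 SD | median | +0.5 SD | +1 SD |
|---|---|---|---|---|---|
| 0.5 | 50.3 → 45.6 (4.7) | 51.5 → 48.3 (3.2) | 50.7 → 48.0 (2.7) | 50.9 → 45.4 (5.5) | 51.0 → 41.5 (9.5) |
| 0.7 | 67.2 → 59.2 (8.0) | 67.2 → 62.5 (4.7) | 67.4 → 63.5 (3.9) | 66.7 → 60.2 (6.5) | 67.1 → 53.1 (14.0) |
| 0.8 | 81.4 → 72.7 (8.7) | 80.9 → 76.1 (4.8) | 81.5 → 76.9 (4.6) | 81.5 → 74.0 (7.5) | 81.5 → 67.0 (14.5) |

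With no true effect (correlation 0.7), rejection rates were 4.5% to 5.2% on both scales.

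**Step 4: adding a retest gain.** The same test is given twice, so both arms may improve with practice. With a 0.5 SD gain in both arms:

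- Correlation 0.8, sample at the median: 81% → 71%, a loss of 10 points.
- Correlation 0.8, sample at +1 SD: 81% → 56%, a loss of 25 points.
- Correlation 0.5, sample 0.5 SD below: 51% → 47–48%.
- Correlation 0.5, sample 1 SD below: 51% → 48%.

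**Step 5: sensitivity to the model.** If change scores are compared without baseline adjustment, the no-gain loss is about 2 to 7 points with the sample between the median and 1 SD below it, and about 11 to 22 points at +1 SD (22 or 25 per arm).

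**Step 6: does the remedy work?** The score in Steps 3 and 4 has no age variation, so it stands for a perfectly age-standardised score. In a separate simulation with a linear age trend, the raw score with baseline and age as covariates came within about 1 point of power of the age-standardised score.

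**The case against.** The strongest reply is that the linear model on percentiles is inferred. The mixed model carries the qualifier that it must be appropriate, the test is chosen after exploration, and the attention section may only describe how the instrument is scored. This stands in part: the article never names the percentile as the model input, and that is only the default reading. But the freedom it leaves concerns the test. The only d2 scale the article ends on is the percentile, and choosing another test does not undo the compression.

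Second, no validity harm is shown. That is correct. A pupil who crosses into an older norm band may get a different percentile for an unchanged score, but randomised arms are affected alike, and type I error holds.

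Third, the loss may be small. That is also correct for a sample near or slightly below the norm median, and nothing in the article says where these adolescents lie.

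Stronger readings are tempting and do not hold:

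- A reader might infer that power for cognition as a whole is lost. The Stroop test is a second cognitive measure and is not converted, and no power is claimed for d2.
- A reader might infer that a retest gain shrinks everyone's improvement. Below the median it need not: a 0.5 SD gain is worth 15.0 points from −1 SD but 19.1 from −0.5 SD.
- A reader might take 19 against 4 points as the trial-level distortion. It contrasts a median pupil with one at about the 93rd percentile, under an assumed gain.

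**Conclusion.** The point holds as a minor matter of efficiency and interpretation in one secondary outcome. The percentile scale makes the mean d2 effect depend on the sample's position on the norm curve, and it gave less power in every setting examined. With baseline adjustment, 25 per arm, a 0.5 SD effect and a correlation of 0.5 to 0.8:

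- about 3 to 5 points lost with the sample at or 0.5 SD below the norm median and no retest gain;
- up to about 10 points at the median with a 0.5 SD retest gain;
- about 25 points only when a +1 SD sample, a 0.5 SD retest gain and a correlation of 0.8 coincide.

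All of these rest on assumed normal norms and on d2 inputs that the article does not give. The direction is secure; the size is not. Nothing here touches the primary outcome or the validity of the comparison.

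**What to change.** Add one sentence to the statistical analysis section: the raw d2 score will be analysed in the planned model with baseline d2 score and age as covariates, and age-specific percentiles will be reported descriptively only. An age-standardised z score is an acceptable alternative and would match the handling of the fitness tests.

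The raw score has to be computed before any percentile can be looked up, so no extra data, visits or participants are needed. The small cost is that the effect is no longer read directly on the norm-percentile scale; tabulated percentiles by group and visit keep that description available.

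This is a cheap improvement, not a condition for the trial's main conclusions.
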